### Reference lab

In order to ensure a standardized and qualified clinical assay, the clinical laboratory of Beijing Ditan Hospital will be assigned as the reference lab for this study. Serum samples collected during the study period should be transported to reference lab for repeating / testing by airway at the end of study.

Hepatitis B virus markers (HBsAg, HBeAg and HBeAb) and virus load (HBV DNA) will be tested at the reference lab. Hepatitis B virus makers will be assayed by Abbott reagent (Abbott Axisim), and the virus load will be determined by real-time PCR **(**PiJi, Shenzhen Co, China with a detection limit of 500 copies/mL**).**

### Clinical laboratory at study centers

Each patient will be screened in the corresponding study center before they are enrolled. The screening testing will be done at clinical laboratory at each center, and will be repeated at the end of the study at the reference lab. The results of screening will be employed as baseline information. The following tests will be carried out during screening at clinical lab of each center:

1. HBeAg、HBsAg、HBsAb 、HBeAb、HBcAb
2. HBV DNA quantity (real-time PCR)
3. Anti-HCV, anti-HIV, anti-HBc

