| Safety endpoints | Adverse events, laboratory testing, systemic and local reactions. |
| Study procedure | - After the protocol being approved by the ethic committee, and inform consenting, patients will be screened and assigned to 30 μg, 60 μg YIC and placebo groups randomly; - Study agents will be given at baseline (0 week), 4th, 8th, 12th, 16th and 20th week; - Treatment will be ended at 20th week, and followed both at 24th week and by 44th -week for efficacy follow-up; - Subjects will be interviewed at baseline, 4th, 8th, 12th, 16th, 20th, 24th, 36th, and 44th week. Each interview will include blood cell count and biochemical liver function testing. Virologic and HBeAg/anti-HBe from samples of all patients will be assayed at the same time for serum at baseline, 12th, 24th, 36th, and 44th week at the reference lab after 44-week follow-up. - Adverse events, and concomitant medication will be recorded at each interview. |

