11. AFP
12. HBV DNA (PCR fluorescent quantitation)

Ten mL blood sample from each screened patient will be required. The serum will be distributed into two vials (2 mL for each), and kept at minus 70 centigrade freezer for repeating assay at reference lab.

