### Definition of endpoints

The virologic response will be assessed four weeks after the end of treatment (week 24) and at the end of follow-up (week 44). HBeAg seroconversion was defined by the loss of HBeAg and the presence of anti-HBe antibody. Suppression of HBV DNA was defined as > 2 log10 decrease of viral load.

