### Primary endpoint

The primary endpoint was defined as loss of HBeAg, or presence of anti-HBe antibody or suppression of HBV DNA.

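### The protocol does not fix one baseline for its primary endpoint, and it counts anti-HBe as a status, so a laboratory difference or a pre-existing state can score as response

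*Protocol*

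**What the plan says.** Two places in the protocol bear on which result is the baseline.

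- **Section 4.4.2 (Clinical laboratory at study centers):** "The screening testing will be done at clinical laboratory at each center, and will be repeated at the end of the study at the reference" (meaning the reference laboratory). The next sentence is "The results of screening will be employed as baseline information", and it leads into a list of tests done at each centre's own laboratory, among them HBeAg, HBeAb and HBV DNA.
- **Synopsis, Study procedure:** virology and HBeAg/anti-HBe "will be assayed at the same time for serum at baseline, 12th, 24th, 36th, and 44th week at the reference lab after 44-week follow-up".

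Section 4.3.2 (Screening) supports the retest: screening serum is "kept at minus 70 centigrade freezer for repeating assay at reference lab". Section 4.4.1 (Reference lab) places the efficacy markers there: "Hepatitis B virus markers (HBsAg, HBeAg and HBeAb) and virus load (HBV DNA) will be tested at the reference lab". The flow chart in Appendix 2 has no virology sample at week 0, so the screening sample is the only baseline sample, and it yields two results.

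The endpoint sections do not choose between them. Section 4.6.1: "Suppression of HBV DNA was defined as > 2 log10 decrease of viral load", with no starting value named. Section 4.6.2: "The primary endpoint was defined as loss of HBeAg, or presence of anti-HBe antibody or suppression of HBV DNA".

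**The concern.** Follow-up virology comes from the reference lab only. Three consequences follow from leaving the baseline open.

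1. **Anti-HBe, under either baseline.** The component is worded as a state. A patient who was HBeAb negative at the centre, and so eligible under section 4.2.1, but is anti-HBe positive on the reference retest of the same serum meets the primary endpoint with no change at all.
2. **HBeAg, if the centre result is the baseline.** A patient positive at the centre and negative on the reference retest appears to have lost HBeAg.
3. **HBV DNA, if the centre result is the baseline.** The log10 change subtracts a reference-lab value from a value produced by one of 12 centre laboratories. The reference PCR is named, with a detection limit of 500 copies/mL. The centre method is described only as real-time PCR.

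The endpoint needs only one of its three components, and planning assumes a 3% placebo rate, so a few such patients matter. The retest comes after week 44, so the choice of baseline could be made with both results in hand.

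**Working it through.** **Inputs from the protocol (sections 6.2 and 6.3, synopsis):** 20% vs 3% for 30 µg and 35% vs 3% for 60 µg; power 80%; level 0.05, two-sided; 78 per arm including 20% dropout; 80 per arm planned for recruitment. Evaluable: 78 × 0.8 = 62.4, taken as 62.

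**The stated sample size.** For the limiting pair, with unpooled variance and 0.05 split over two comparisons:

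n = (2.241 + 0.842)² × (0.20 × 0.80 + 0.03 × 0.97) / 0.17² = 62.2, and 62.2 / 0.8 = 77.7, or 78.

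This is one variant that reproduces 78; the protocol does not say which was used. The figure is not in dispute here.

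**Serological route.** Let d be the share of patients who meet a component from the start because of discordance. Assume that d is equal in all arms and that the state persists to assessment. The documents give no value for d. The observed rate is d + (1 − d)p. At d = 5%:

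- placebo: 0.05 + 0.95 × 0.03 = 0.0785
- 30 µg: 0.05 + 0.95 × 0.20 = 0.240

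Exact power for 30 µg at two-sided 0.05 is summed over the two binomial distributions. The lower figure uses Fisher's test throughout. The upper uses chi-square, with Fisher's test when an expected count is below 5 (the protocol does not define sparse).

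| d (assumed) | Placebo | 30 µg | Power, 62 per arm | Power, 80 per arm |
| --- | --- | --- | --- | --- |
| 0 | 3.0% | 20.0% | 82–88% | 93–95% |
| 2% | 4.9% | 21.6% | 73–81% | 86–90% |
| 5% | 7.9% | 24.0% | 62–70% | 76–82% |
| 10% | 12.7% | 28.0% | 48–56% | 62–68% |

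Both sizes are shown because the full analysis set keeps anyone with one post-injection efficacy evaluation and uses LOCF, so its size may lie between them. For 60 µg, the lowest power in this grid is 94–96% (d = 10%, 62 per arm).

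**HBV DNA route (centre baseline only).** Let b be the amount, in log10, by which the centre assay reads above the reference assay, and s the SD of the observed difference when there is no true mean change. Both are assumed.

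P(apparent fall > 2) = 1 − Φ((2 − b)/s)

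| s | b = 0 | b = 0.5 | b = 1.0 | b = 1.5 |
| --- | --- | --- | --- | --- |
| 0.5 | 0.0% | 0.1% | 2.3% | 16% |
| 0.7 | 0.2% | 1.6% | 7.7% | 24% |
| 1.0 | 2.3% | 6.7% | 16% | 31% |

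At s = 1.0, 2.3% arises with no laboratory offset. If the centre assay reads lower, false falls become rarer and true falls can be hidden.

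**The case against.** A reader might infer that the protocol flatly contradicts itself, or that it commits to centre values as the efficacy baseline. The text does not go that far. Section 4.4.2 says in the sentence before that screening tests are repeated at the reference lab, so the screening results may include that repeat. The list that follows also covers liver and renal function, blood count and urine, so the sentence may mean only that the screening draw serves as the baseline time point. The synopsis, section 4.3.2 and section 4.4.1 all point to the reference lab, and retesting baseline serum alongside follow-up would have little purpose if centre values were used. This stands: it is an unresolved inconsistency. But even on the generous reading two results exist, and nothing says which one counts.

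It can also be said that loss of HBeAg implies earlier presence, and that the handling of discordant patients belongs in an analysis plan, which is not shown. The first is fair once the baseline is the reference result. The second does not rescue the anti-HBe component, because section 4.6.2 itself fixes it as a status, and adopting the reference baseline alone would leave that unchanged.

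Finally, randomization is blocked within centre (section 7) and assessment is blinded (section 4.3.7), so the error should be about equal across arms. That stands in full.

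**Conclusion.** The point holds as an unfixed baseline combined with a component worded as a status. The expected effect is a higher placebo rate, a diluted treatment difference and response that depends partly on centre.

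Three stronger conclusions are not supported. Type I error is not inflated, because equal error in all arms leaves the null comparison intact. The trial is not shown to be underpowered: no discordance rate is documented, and across 2–5% discordance 30 µg power runs from 62% to 90%, depending on the test and on 62 or 80 per arm. Nor can a fall of more than 2 log10 be put down to a change of laboratory in general: that route is small unless the offset nears 1 log10 or the SD of the change is about 1.0.

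The serological route is the stronger one because it needs no assay offset. Any loss falls mainly on the 30 µg comparison, the dose that section 2.2 adds because it might be the optimal one.

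**What to change.** 1. In sections 4.4.2 and 4.6.1, state that baseline HBV DNA, HBeAg and anti-HBe for every efficacy endpoint are the reference-lab results on the stored screening serum, assayed with the follow-up samples as the synopsis already plans. Centre results serve eligibility only.
2. In sections 4.6.1 and 4.6.2, define each component as a change from that baseline: HBeAg positive to negative, anti-HBe negative to positive, HBV DNA down by more than 2 log10.
3. Fix before unblinding how patients discordant on retest are analysed. One option is to keep them in the full analysis set but not count them as responders on a component already met at baseline. Other rules are defensible; what matters is that one is set in advance.

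The cost is wording. The serum is already to be stored and the retest is already planned, so no sample, visit or assay is added, and the stated sample size need not change on this account.

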4. AFP
5. Liver function: ALT, AST, TBil, DBil, TP, ALB, and AKP
6. PTA
7. Renal function: BUN, Cr, and Electrolytes (K、Na、Cl)
8. Blood cell count: WBC, RBC, Hb, and PLT
9. Uric testing

### Testing during follow-up period

In each study center, liver function, renal function, Electrolytes, blood cell count and uric testing will be performed for all enrolled patients at week 4, 8, 12, 16, 20, 24, 36 and 44.

## Safety measurement

Systemic symptoms, local reactions and allergic reactions will be detected within 30 minutes after each injection at each research center, and through diary card between two visits for all enrolled patients.

1. Local reactions: swelling, pain, edema and redness at inject site;
2. Systemic symptoms: allergic reactions, fever, erythra, pruritus, nettle rash, joint pain, **a**rthritis, obvious abnormal of hemogram, gastrointestinal reactions, renal function abnormal, autoimmune disorder, hypersensitive response.

### Definition of adverse events

*Adverse event following immunization (AEFI)*

A medical incident that takes place after vaccination, causes concern and is believed to be caused by the immunization. Reported adverse events may be either causally or coincidentally related to the vaccination.

*Coincidental AEFI*

A medical incident that would have occurred whether the individual had received an immunization prior to the incident or not.

### Surveillance of adverse events following injections

A surveillance system will be implemented to document the safety profile of the study agents during the study period. Surveillance of vaccine safety will be carried out following the WHO guidelines. At each study center, all adverse events either observed by the investigator or reported by the patients spontaneously will be evaluated by the investigator. Type III allergic reactions, such as fever, redness, pruritus, rash, joint pain and arthritis should be included in the AEs observation in this study.

The following surveillance methods will be applied to detect and record adverse events:

*Observation 30 minutes after vaccination*

All patients will be asked to remain at the vaccination site for 30 minutes immediately after vaccination to observe the immediate adverse events. Immediate serious adverse events will be treated following the WHO guidelines and recorded in the Serious Adverse Event Report Form by trained investigators. Each study center will be equipped with basic emergency equipment in case of an immediate SAE.

*Adverse events between two injections*

The potential AEs occurs between two visits will be recorded to the diary card by patients. At the beginning of each visit, investigators should query patients about AEs may occur during the two visits, and collect the diary card from last visit.

### Recording adverse events

All adverse events will be recorded as an adverse event on the adverse event forms, irrespective of severity of whether or not they are considered vaccination-related. The nature of each event, date and time (where appropriate) of onset, outcome and intensity should be established using clear medical terms.

### Criteria of adverse events intensity

When reporting adverse events, the intensity will be described as mild, moderate and severe according to the following criteria:

1. Mild: easily tolerated; causing minimal discomfort; not interfering normal everyday activities;
2. Moderate: Sufficiently discomforting to interfere with normal everyday activities;
3. Severe: Prevents normal everyday activities

Please notice the difference between the term “severe” and term “serious”. They are not synonymous. For regulatory definition, “serious” is used to describe the “seriousness”, and “severe” relates to “intensity”. Headache could be severe, but could not be SAE, unless it meets the SAE criteria.

### Criteria of adverse events causality

Causality of adverse events to injections and concomitant medication should be established by investigators according to following criteria:

1. Very likely/certain

A clinical event with a plausible relationship to vaccine administration and which cannot be expected by concurrent disease or other drugs or chemicals.

1. Probable

A clinical event with a reasonable time relationship to vaccine administration; is unlikely to be attributed to concurrent disease or other drugs or chemicals.

1. Possible

A clinical event with a reasonable time relationship to vaccine administration, but which could also be explained by concurrent disease or other drugs or chemicals.

1. Unlikely

A clinical event whose time relationship to vaccine administration makes a causal connection improbable, but which could be plausibly explained by underlying disease or other drugs or chemicals.

1. Unrelated

A clinical event with an incompatible time relationship and which could be explained by underlying disease or other drugs or chemicals.

1. Unclassifiable

A clinical event with insufficient information to permit assessment and identification of the cause.

### Measures taken after abnormal laboratory tests

When unexplainable abnormal laboratory test appears, the test must be repeated immediately , the patients should be followed-up constantly till either the abnormal test has resolved, or could be explained from investigator’s point of view. The definitive explanation should be recorded in the CRFs.

### Treatment and follow-up of adverse events

Any adverse event must be treated with acceptable method. Investigators must report and discuss with SPONSOR when a method repelling with study agent has to be implemented, since this activity will cause premature withdrawal. All adverse events should be followed-up until the event has: resolved or subsided or stabilized or disappeared or the event is otherwise explained.

### Definition for serious adverse event (SAE)

Serious adverse event is defined as any untoward medical occurrence that:

1. Results in death
2. Requires initial or prolonged inpatient hospitalization
3. Is life-threatening
4. Results in severe or permanent disability

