### Discontinuation/Withdrawal

Any patient who had signed a consent form, and meet the following criteria will be defined as premature withdrawal.

1. Patients who request to quit themselves;
2. Patients who violate the study protocol;
3. Patients who become pregnancy;
4. Patients who are unblinded due to SAE;
5. Patientsduring the treatment period who developed the following symptoms
   - - - Hepatic cirrhosis
       - Hepatic failure
       - And hepatoma.

If the withdrawal occurs due to the adverse events or abnormal laboratory tests, details should be recorded in the CRFs.

- 1. Laboratory assay

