### Unscheduled pregnancy

Any pregnancies which occur during study period should be reported to corresponding investigator, and all study related-treatment should be stopped consequently. Investigator should report to both CRO and SPONSOR using specific-pregnancy form. The pregnant patient should be followed-up till delivery, the outcome of pregnancy and delivery should be reported to both CRO and SPONSOR. The pregnancy occurs with participant’s wife also should be reported and followed.

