### Recording and reporting of SAE

The investigator is responsible for the detection and documentation of events meeting the criteria and definition of a serious adverse event (SAE) as provided in this protocol. Each patient will be instructed to contact the investigator immediately should the subject manifest any signs or symptoms they perceive as serious.

SAEs will be reported concurrently to CRO, SPONSOR, Principle Investigator, IRB, and SFDA within 24 hours, once the investigator determines that the event meets the protocol definition of a SAE. The SAE Form will always be completed as thoroughly as possible with all available details of the event, signed by the investigator (or designee), and will always provide an assessment of causality at the time of the initial report.

After the initial SAE report, the investigator is required toactively follow each subject and provide further information to the CRO, SPONSOR, Principle Investigator, IRB, and SFDA on the subject’s condition. Investigators will follow-up subjects with SAEs until the event has: resolved or subsided or stabilized or disappeared or the event is otherwise explained, or the subject is lost to follow-up.

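### The four-criterion SAE definition omits congenital anomalies and medically important events, so a non-disabling birth defect or a cirrhosis diagnosed without admission need not be reported to the IRB and SFDA within 24 hours

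*Protocol*

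**What the plan says.** All references are to the protocol.

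- **Section 4.5.8 (SAE definition).** The lead-in is "Serious adverse event is defined as any untoward medical occurrence that". Four items follow: death; "Requires initial or prolonged inpatient hospitalization"; threat to life; and "Results in severe or permanent disability". The list ends there.
- **Section 4.5.10 (SAE reporting).** "SAEs will be reported concurrently to CRO, SPONSOR, Principle Investigator, IRB, and SFDA within 24 hours". The clock starts "once the investigator determines that the event meets the protocol definition of a SAE".
- **Section 4.5.9 (pregnancy).** "The pregnant patient should be followed-up till delivery, the outcome of pregnancy and delivery should be reported to both CRO and SPONSOR". A pregnancy in a participant's wife must also be reported and followed. No deadline is given for the outcome, and neither the IRB nor the SFDA is named.
- **Section 4.3.8 (withdrawal).** Cirrhosis, hepatic failure or hepatoma developing during the treatment period is a ground for premature withdrawal. The reporting instruction there is: "If the withdrawal occurs due to the adverse events or abnormal laboratory tests, details should be recorded in the CRFs".

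**The concern.** The definition in 4.5.8 decides which events go to the IRB and SFDA within a day and which do not. It is silent on two kinds of event that the protocol itself treats as important elsewhere.

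The first is an abnormal pregnancy outcome. Section 4.2.1 bars birth plans for both sexes until 3 months after completion, and 4.5.9 follows a patient's pregnancy to delivery. A birth defect is a main reason for such follow-up, yet no SAE criterion names it.

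The second is a new major liver diagnosis. Section 4.2.2 excludes confirmed or suspected cirrhosis and primary hepatic carcinoma at entry, so either one arising on treatment is newly identified. Section 4.3.8 ends participation for it, but an outpatient diagnosis need not meet any of the four criteria.

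At stake is the speed and consistency of safety oversight in a trial of an immune-complex vaccine in patients with liver disease.

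**Working it through.** No arithmetic applies; the point rests on no sample size, error rate or event count. The check has three steps.

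**Step 1: is the list closed?** Section 4.5.8 gives four criteria. None names a congenital anomaly and none is a residual item for medically important events. Two other sections treat the list as exhaustive. Section 4.5.4 explains that a severe event is not an SAE unless it meets the SAE criteria, and 4.5.10 ties the 24-hour report to the protocol's own definition.

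**Step 2: which events fall outside it?**

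| Event | Death | Admission | Life-threatening | Severe or permanent disability | SAE in its own right? |
|---|---|---|---|---|---|
| Birth defect in a surviving infant, not disabling, no admission, no threat to life | no | no | no | no | no |
| Birth defect judged disabling | no | may vary | may vary | yes | yes, by judgement |
| Cirrhosis found at an outpatient visit | no | no | not evidently | not evidently | no |
| Hepatoma found at an outpatient visit | no | no | open to judgement | open to judgement | depends on the site |

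The protocol defines neither threat to life nor disability further, so the second and fourth rows are left to each investigator. Hepatic failure, the third liver outcome in 4.3.8, is the least likely of the three to escape the existing criteria.

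**Step 3: does another section provide the expedited route?**

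| Section | What it requires | Reaches IRB and SFDA within 24 hours? |
|---|---|---|
| 4.3.8 Withdrawal | case report form details | no |
| 4.5.3 Recording adverse events | adverse event form, whatever the severity or relation to vaccination | no |
| 4.5.9 Pregnancy | form and outcome to CRO and sponsor | no |
| 4.5.11 Important noticeable event | withdrawal to be resolved and recorded; no recipient or deadline | no |
| 4.5.12 Causality procedure | joint assessment, with referral to an outside committee on disagreement, for SAEs only | no |
| 10.1 Protocol review | adverse events in a progress report for annual IRB review | no |

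No route to the IRB and SFDA within 24 hours exists outside the SAE definition. The definition also governs 4.5.12, so an event outside it has no claim on the joint review or the referral.

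Two smaller effects follow. The diary card in 4.3.6 for the week 36 and 44 visits is described as a record of serious events, although the Appendix 2 flow chart keeps general adverse event enquiry going at those visits. The sponsor's cost commitment in 10.8 is worded for vaccine-related serious events, although 10.5.1 separately offers free treatment for related adverse events.

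**The case against.** The strongest reply is that these events are captured anyway. Section 4.5.3 records every adverse event; 4.5.5 and 4.5.7 require a causality grade and follow-up; 4.5.11 requires withdrawals to be resolved and recorded; monitors check adverse event documentation under section 11; and the IRB sees adverse events in its progress report. Pregnancy has its own form and follow-up. This stands: the loss is of speed and classification, not of capture.

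It also disposes of a stronger reading. A reader might infer that an SAE table by arm would miss these events, or that each missed event would change a comparison between arms. The protocol describes no such table or comparison. Section 6.1 compares the occurrence of adverse events among the three groups in the safety set, and a new cirrhosis or hepatoma recorded for a patient in that set counts there whether or not it is labelled serious.

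A second reply is that the text does not categorically exclude these events. An investigator could call a hepatoma life-threatening or a birth defect a permanent disability. That is correct and limits the claim to events that are not SAEs in their own right. It does not remove the problem, because the same event could then be classed differently at different sites.

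A third reply is that the scenarios are narrow. Cirrhosis and suspected carcinoma are excluded at entry; the liver withdrawal rule covers the treatment period only; pregnancy is excluded and tested for; and only the patient's own pregnancy is expressly followed to delivery. All of this stands and argues for a low expected number of cases. The protocol gives no rate.

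Finally, grounds for withdrawal and criteria for seriousness serve different purposes, so 4.3.8 and 4.5.8 do not contradict each other. That is also right. The point is a definition that gives a worse result than it could, not an inconsistency.

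**Conclusion.** The point holds in a limited form. Followed as written, the protocol leaves a non-disabling birth defect and an outpatient-diagnosed cirrhosis off the 24-hour clock to the IRB and SFDA and outside the SAE causality review. It also leaves the classification of a hepatoma, or of a possibly disabling anomaly, to each of the 12 centres.

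No statistical figure changes, and the adverse event comparison in 6.1 is unaffected. The number of events involved cannot be estimated from the document and is probably small. The conclusion assumes that the event does not otherwise lead to admission, death or a judged threat to life; where it does, the existing criteria already apply. The change is worth making because it closes a safety-reporting gap at very little cost.

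**What to change.** In 4.5.8 add two criteria: (5) congenital anomaly or birth defect; (6) any other medically important event, expressly naming the hepatic cirrhosis, hepatic failure and hepatoma of 4.3.8 item 5. Naming hepatic failure with the other two avoids a split classification of the three outcomes.

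In 4.5.9 state that an abnormal outcome of a patient's or a partner's pregnancy is reported through 4.5.10, in addition to the existing report to the CRO and sponsor. A cross-reference from 4.3.8 to 4.5.10 would align the withdrawal text.

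The cost is two definition lines, one routing sentence and slightly more expedited reports. Dose, schedule, withdrawal rules and clinical care are untouched.
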